## Abstract

**Introduction:**

Rock climbing is a rapidly growing sport in which performance may be affected by participant’s weight and leanness, and there may be pressure on athletes with respect to their eating behaviour and body weight. However, there is sparse research performed on climbers, constituting a knowledge gap which the present study aims to fill. The primary outcomes of the study are to examine disordered eating and overuse injuries in rock climbers. Secondary variables are body image, indicators of relative energy deficiency, mental health problems, compulsive training, perfectionism, sleep quality and bone density.

**Method and analysis:**

This prospective longitudinal study aims to recruit Swedish competitive rock climbers (>13 years) via the Swedish Climbing Federation. A non-athlete control group will be recruited via social media (n=equal of the climbing group). Data will be collected using streamlined validated web-based questionnaires with three follow-ups over 2 years. Inclusion criteria for rock climbers will be a minimum advanced level according to International Rock-Climbing Research Association. The non-athlete control group is matched for age and gender. Exclusion criteria are having competed at an elite level in any sport as well as training more often than twice per week. Statistical analyses will include multinominal logistic regression, multivariate analysis of variance (MANOVA) and structural equation modelling (SEM). We will assess effect measure modification when relevant and conduct sensitivity analyses to assess the impact of lost to follow-up.

**Ethics and dissemination:**

The Rock-Climbers’ Longitudinal attitudes towards Injuries, Mental health and Body image study, CLIMB, was approved by the Swedish ethics authority (2021-05557-01). Results will be disseminated through peer-reviewed research papers, reports, research conferences, student theses and stakeholder communications.

**Trial registration number:**

NCT05587270.

STRENGTHS AND LIMITATIONS OF THIS STUDYLongitudinal assessment of disturbed eating, mental health status, overuse injuries, bone health and symptoms indicative of relative energy deficiency in advanced rock-rock climbers and normal controls.The use of valid and reliable instruments and measurement methods and the large number of potential confounders will improve the internal validity of the estimated associations.The use of dual-energy X-ray absorptiometry complements the participant’s self-report data with objective measurements on bone health.Multivariate statistical analysis will be executed to answer the research questions.One limitation is the use of self-report questionnaires only rather than the combination of self-report and structured interviews.

## Introduction

Rock climbing as a sport places high demands on strength, mobility and endurance of the athlete. In sports, like rock climbing, weight and leanness may play an important role for achievement, and there may be pressure on athletes with respect to their eating behaviour and body weight.^1^ In a study by Giel *et al*^2^ on elite athletes in 51 Olympic sport disciplines, the results indicated higher rates of eating disorders (EDs) symptoms among athletes in weight dependent sports as well as higher levels of mental health problems. However, there is limited evidence and mixed results in the literature on ED pathology in elite athletes.

Rock climbing has in recent years gained increased popularity as a recreational and competitive sport, as reflected by a rapid increase of practitioners, media coverage and the recent inclusion of the sport in the Olympics of 2020 and 2024. Research on climbing related disordered eating (DE) and relative energy deficiency in sport (RED-S) is sparse. The recent increase in the numbers of rock climbers, both competing athletes and recreational rock climbers, has brought attention to health issues related to climbing. Especially for high-performance climbing, relative strength to weight ratio has been shown to be of importance for performance resulting in lean body shapes, commonly with low Body Mass Index (BMI), fat percentages and low calorie intakes.^3^

Compulsive exercise (CE) consists of maladaptive compensatory behaviours and serves as a strategy for emotion regulation—often closely linked to eating disturbances.^16^ Weight-affecting behaviours in non-clinical groups have demonstrated addictive qualities that aid the understanding of why these behaviours are difficult to change.^16^ Weight-affecting behaviours such as CE have a marked negative effect on psychological and physiological health,^17^ and emotion dysregulation has been suggested to trigger these behaviours.^18^ A previous study of university students indicated a negative association between symptoms of depression and CE for weight control, and a positive association for body dissatisfaction and depression.^19^ These results are in line with studies suggesting excessive exercise to be associated with different psychological traits where poor emotion regulation and compulsivity are two of them.^20^ This may suggest that CE serves as a negatively reinforced behaviour, serving as short-term alleviation of discomfort. Furthermore, exercising for regulation of negative emotion has been consistently identified as a contributory factor to the development and maintenance of EDs.^21^ This contribution does not lie specifically in the presence of negative emotion, but rather in the CE habits that develop as an outlet for these emotions, which in turn is a risk factor for developing disturbed eating. CE is characterised by an inability or unwillingness to cut down or stop the behaviour despite adverse health consequences.

Body dissatisfaction is associated with a drive for thinness,^22 23^ dieting^24^ and DE patterns.^24 25^ The exposure to physical ideals has been seen to have a stronger immediate impact on girls than boys,^26^ and preoccupation with weight, maladaptive methods for weight control and body dissatisfaction are known precursors of more serious clinical EDs, both among athletes and in the general population.^11 12 27^ However, athletes from leanness-focused sports report higher rates of eating disturbances compared with athletes from non-weight sensitive sports.^9^

Empirical research suggests that elite athletes involved in lean-sensitive or weight-sensitive sports are at elevated risk of developing an ED.^1 28^ In 2020, one of the first papers on EDs and climbing ability was published, which assessed 604 rock climbers (ages 32±9 years). It presented demographic data according to the International Rock-Climbing Research Association’s (IRCRA) directives.^29^ The results showed that higher level rock climbers had significantly lower BMI among both genders, and that 8.6% of the rock climbers reported DE behaviours. Additionally, 4.2% reported having been treated for an ED and there was an increased risk for EDs among female elite rock climbers compared with males.^30^ Strand^31^ states in a study of conversations in climbing communities that conversations related to achieving or maintaining low weight and lean body shape for performance enhancement purposes are common. Furthermore, Strand advises clinicians to be attentive to ‘weight talk’ in the climbing community.

Our main hypothesis is that elite and advanced rock climbers will present more DE symptoms compared with controls, with elite rock climbers showing more symptoms than advanced rock climbers. A secondary hypothesis is that rock climbers who report more eating disturbances will present with higher levels of health problems including decreased bone density, CE, depression, body dissatisfaction, menstrual disturbances and more overuse injuries as compared with rock climbers with less symptoms of eating disturbances, as these secondary variables are correlates of EDs.^32^ We expect these patterns to be stable over time. The authors will also examine the gender differences in these categories and expect, for example, to find higher percentages of DE among women than men, following the pattern of the presented literature. At the time of writing, there exists sparse research on the connection between rock climbing, DE and energy deficiency. The presented hypotheses are therefore largely grounded on findings in other sports with similar bodily and/or weight requirements, such as ballet, figure skating and gymnastics. Due to the rapidly increasing popularity of recreational and competitive climbing, longitudinal cohort studies are, therefore, urgently needed to understand the aetiology of health problems related to EDs in rock climbers in particular. Studies that identify risk and prognostic factors are required to develop health promotion and disease prevention strategies, which ultimately can reduce the burden of disease in rock climbers worldwide.

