### Statistical methods

#### Sample size

No previous data on injury incidence based on overuse injuries exist for rock climbers. Based on previous retrospective data from rock climbers,^49^ using a power of 80%, a significance level of 5% and an expected relative risk of 1.5 for the primary outcome, we calculated that approximately 55 participants were needed in each group (rock climbers and control group).

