### Data analysis plan

Multinominal logistic regression analyses will be used to determine the associations between each of the exposures and trajectories of outcomes. The associations as ORs and 95% CIs will be reported. Bivariate models to measure the crude associations between the exposures and trajectories will be built.

The differences between the rock climbers and controls regarding the above-mentioned outcome measure ED will be analysed using multivariate analysis of variance (MANOVA). Both within-group and between-group analysis will be conducted. Further analyses among rock climbers with high ED versus low ED will be compared in relation to bone density, injuries, mental health and symptoms of RED-S. The MANOVA will be used for that purpose. A one-way repeated measures ANOVA will be used to identify changes over the 2-year span in the two groups of rock climbers with high ED versus low ED. In cases where overall significant changes are detected, post hoc analysis will be applied to specify where the between-group differences exist.

Structural equation modelling will be used at a later stage to investigate if the variables body image, injuries, mental illness, sports environment, bone density (from baseline) and EDs can predict injuries.

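### The expectation that the high- versus low-ED patterns stay stable is paired with a one-way repeated-measures ANOVA that seeks change within each group, which cannot support stability

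*Protocol article*

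**What the plan says.** The Introduction states a main hypothesis (climbers against controls, elite against advanced climbers, on disordered eating) and a secondary one (climbers with more eating disturbance against those with less, on health correlates). It then says: "We expect these patterns to be stable over time".

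The Data analysis plan gives one analysis of mean change: "A one-way repeated measures ANOVA will be used to identify changes over the 2-year span in the two groups of rock climbers", the two groups being high ED and low ED. The next step is conditional: "In cases where overall significant changes are detected, post hoc analysis will be applied to specify where the between-group differences exist".

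The other longitudinal analysis is of a different kind: "Multinominal logistic regression analyses will be used to determine the associations between each of the exposures and trajectories of outcomes". It relates exposures to trajectories and does not ask whether a group difference stays constant.

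Under Sample size, "approximately 55 participants were needed in each group (rock climbers and control group"). No threshold for high against low ED is given. Under Study design and participants, the whole eligible population is invited and controls are not followed up.

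**The concern.** An expectation of stability is a no-change hypothesis, whereas the named ANOVA is built to detect change. Two things go wrong.

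- **Direction of proof.** A significant F counts against stability. A non-significant F says only that change was not shown. The smaller the group and the heavier the drop-out, the more likely the result that looks like the predicted one.
- **Wrong contrast.** The secondary hypothesis concerns a difference between climbers with more and with less disturbance. A one-way ANOVA run within each group has no between-group term, so it does not estimate whether that difference changes. The follow-up step speaks of locating between-group differences, which this model does not contain.

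At stake is the longitudinal conclusion: whether the health correlates of disturbed eating persist, worsen or resolve over 2 years.

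**Working it through.** **1. The plan's own figure.** The basis of the 55 is "using a power of 80%, a significance level of 5% and an expected relative risk of 1.5 for the primary outcome". No control risk is given. With the usual two-sided two-proportion formula, n per group is 58 at a control risk of 0.50 and 52 at 0.52, so 55 corresponds to about 0.51. It can be back-solved but not verified, and it does not concern change over time.

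**2. Size of the high-ED group, assuming a disordered-eating cut-off.** The rates are those the article cites.
- All climbers (Introduction): 55 × 8.6% = 4.7, about 5.
- Women (Discussion): 55 × 16.5% = 9.1, about 9. This applies a female-only rate to a mixed cohort, so it is an upper figure for the expected count.
- Men (Discussion): 55 × 6.3% = 3.5.

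**3. Chance that the within-group ANOVA misses a 0.5-SD change, for an outcome not used to form the groups.** Occasions are baseline, 6 months, 1 and 2 years. Noncentrality is λ = n Σ(μ_j − μ̄)² / (1 − r), with 3 and 3(n − 1) degrees of freedom, alpha 0.05 and equal correlation r between surveys. The values 0.5 and 0.7 for r are assumed. The value 0.89 is the EDE-Q test-retest figure, with no interval stated, and is not a 2-year correlation for the other outcomes.
- Gradual change (0, 0.125, 0.25, 0.5): Σ = 0.1367. For n = 5, r = 0.5: λ = 5 × 0.1367 / 0.5 = 1.37, power 12%.
- Step change (0, 0.5, 0.5, 0.5): Σ = 0.1875. For n = 9, r = 0.7: λ = 9 × 0.1875 / 0.3 = 5.63, power 42%.

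Miss rates over these two shapes:

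| n | r = 0.5 | r = 0.7 | r = 0.89 |
|---|---|---|---|
| 5 | 86–88% | 78–83% | 47–60% |
| 9 | 74–80% | 58–68% | 13–26% |

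For the low-ED group (n = 46 to 50), power is about 85% or more at r of at least 0.5.

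**4. The contrast the hypothesis needs: high-minus-low difference in change from baseline to 2 years.** SE = √(2(1 − r)) × √(1/n₁ + 1/n₂) in SD units, and the 95% half-width is t × SE. For 5 v 50 at r = 0.5: 1.0 × √(0.2 + 0.02) = 0.469, and 2.006 × 0.469 = 0.94. The miss rate for a true 0.5-SD difference comes from the noncentral t.

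| Split | Half-width (SD), r = 0.5 / 0.7 / 0.89 | Miss rate |
|---|---|---|
| 5 v 50 | 0.94 / 0.73 / 0.44 | 82 / 73 / 39% |
| 9 v 46 | 0.73 / 0.57 / 0.34 | 73 / 59 / 18% |
| 17 v 183 (200 climbers, 8.6%) | 0.50 / 0.39 / 0.23 | 50 / 28 / 1% |

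**5. The EDE-Q behaves differently.** If high ED is picked on the baseline EDE-Q and scores are normal, that group starts φ(c)/p SD above the mean, where p is the proportion selected and c the cut-off. This is 1.83 SD at p = 8.6% and 1.50 SD at p = 16.5%. With no true change it is expected to fall by (1 − r) times that: 0.91, 0.55 and 0.20 SD at p = 8.6%, and 0.75, 0.45 and 0.17 SD at p = 16.5%, for r = 0.5, 0.7 and 0.89. Simulating the four-occasion ANOVA with this selection (10,000 replicates) gives:

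| | r = 0.5 / 0.7 / 0.89, n = 5 | n = 9 |
|---|---|---|
| Significant with no true change | 46 / 27 / 11% | 63 / 38 / 15% |
| True 0.5-SD recovery missed | 26 / 35 / 30% | 6 / 12 / 6% |
| True 0.5-SD worsening missed | 73 / 84 / 76% | 65 / 77 / 49% |

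So the miss rates in step 3 do not carry over to the EDE-Q.

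**The case against.** Several stronger readings are tempting, and the article does not support them.

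- **That the authors will take p > 0.05 as stability.** No passage says so. The article only leaves no other criterion on the page.
- **That a moderate change will be missed most of the time.** This depends on a correlation the article does not give. With 9 climbers and r = 0.89, the miss rate is at most 26%. High ED has no stated threshold, and a median split of 55 would give about 27. Further, 55 is a number needed and not a cap. The low-ED group is adequately powered at r of at least 0.5.
- **That non-significance is to be expected for every outcome.** It is not for the EDE-Q, where selection on baseline pushes towards apparent change.

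Two broader objections deserve an answer. First, stable may mean only that the high-low difference is found again later. That would support persistence in direction, but not constancy, and the article does not assign such a repeated comparison to the stability expectation. Second, a margin and an interpretation rule are commonly left to the full protocol or SAP. That is fair, and the missing margin alone would be no finding. What stands is that the article itself states an expectation and names a test that cannot bear on it in the required direction or for the required contrast.

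**Conclusion.** The point holds in limited form. The named ANOVA can support neither stability of group means nor stability of the high-low difference; this follows from the text without any assumed figure. Stability of the climber-control difference cannot be examined at all, because controls are not followed.

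The size is conditional. With about 55 climbers, a disordered-eating cut-off, and correlations of 0.5 to 0.7, a 0.5-SD change in a health correlate would be missed in 58% to 88% of cases in the high-ED group. Higher correlations or more climbers reduce this, and drop-out, which the Discussion acknowledges, increases it. For the EDE-Q the more likely error is spurious change, or a masked worsening. This is worth correcting before the 2-year data are analysed; it does not undermine the baseline comparisons.

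**What to change.** In the Data analysis plan:

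1. For the health correlates measured at follow-up, estimate the high-minus-low difference over time (a group-by-time term) with its 95% CI. Bone density is measured at baseline only and falls outside this.
2. Pre-state a margin for each outcome. Conclude stability only if the whole CI lies inside it, and otherwise report the result as inconclusive. The 0.5 SD used here is illustrative.
3. State that a non-significant ANOVA will not be taken as evidence of stability.
4. State how high and low ED are defined.
5. For the EDE-Q, do not judge stability from raw change from baseline in groups selected on that baseline. Use the whole climber cohort or the post-baseline surveys.

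The cost is wording and one extra interval per outcome, from data already being collected. The downside is that, at about 55 climbers, the result will often be inconclusive: at correlations of 0.5 to 0.7 the expected half-widths for 5 v 50 and 9 v 46 (0.57 to 0.94 SD) exceed a 0.5-SD margin.

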### Patient and public involvement

None.

### Instruments

The first portion of the questionnaire aims to confirm that participants are eligible for inclusion, with a climbing level of advanced or above as classified by IRCRA. Demographic data will be gathered and reported including factors such as age, time practising the sport, amount of weekly training hours, climbing level and gender. Symptoms related to eating disturbances, RED-S, body image, compulsive training, perfectionism, mental health problems, sleep quality, overuse injuries and menstrual dysfunction will thereafter be measured (see table 1).

**Table 1 T1:** Measurements in the CLIMB-study.

Variable	Instrument	Baseline	Follow-up (6 months, 1, 2, 3 and 5 years postbaseline)
Eating disorder symptoms	The Eating Disorders Questionnaire (Fairburn and Beglin, 1994)^33^	X	X
Overuse injuries	The Oslo Sports Trauma Research Centre Overuse Injury Questionnaire (Clarsen *et al*, 2013)^35^	X	X
Perfectionism	The Frost Multidimensional Perfectionism Scale (Frost *et al)*^36^	X	X
Compulsive training	The Compulsive Exercise Test (Taranis *et al*)^39^	X	X
Body dissatisfaction	Body Shape Questionnaire, brief version (Welch *et al*)^41^	X	X
Mental health	Depression Anxiety Stress Scale-21 (Lovibond and Lovibond)^44^	X	X
Sleep quality	The Pittsburg Sleep Quality Index (Carpenter and Andrykowski)^46^	X	X
Symptoms of relative energy deficiency	Relative Energy Deficiency in Sports: RED-S (Edlund Health Q, Edlund, 2020)^50^	X	X
Physical activity and sedentary behaviour	Indicator Questions from the Swedish National Board of Health and Welfare	X*	
Bone density	DEXA	X†	

*Physical activity and sedentary behaviour will only be performed on the control group.

†DEXA will only be performed on a proportion of rock climbers.

DEXA, dual-energy X-ray absorptiometry.

In addition to the web-based questionnaire, bone health using dual-energy X-ray absorptiometry (DEXA) will be measured for climbing participants at baseline.

#### Eating Disorders Examination Questionnaire

DE will be measured by the Eating Disorders Examination Questionnaire (EDE-Q 6.0),^33^ which is validated and includes 36 questions and records symptoms during the 28 days prior to filling in the questionnaire (eg, ‘Have you been deliberately trying to limit the amount of food you eat to influence your shape or weight (whether or not you have succeeded)?’. EDE-Q consists of four subscales (Restriction Scale, Eating Concern, Figure Concern and Weight Concern) as well as a score indicating global level of EDs symptoms. A cut-off score of >2.5 will be used as indicative of DE and >4.0 for EDs. EDE-Q has demonstrated adequate test–retest reliability (r=0.89) and internal consistency (α=0.85).^34^

#### The Oslo Sports Trauma Research Centre Overuse Injury Questionnaire

The Oslo Sports Trauma Research Centre Overuse Injury Questionnaire (OSTRC-O)^35^ is used to gauge the effects of pain and injuries on participation in sport. The original questionnaire measures injuries in the knee, shoulder, foot/lower leg and lower back. Since climbing is a sport relying heavily on chest, neck, finger, hand and arm strength, additional items targeting these body parts will be added to the instrument. The questionnaire consists of four questions regarding the athlete’s participation in training and competition, reduced training, performance and pain the asked period (eg, ‘have you had any difficulties participating in normal training and competition due to (physical) problems last week?’ The alternatives for responses are ranged from ‘full participation without problems’, ‘full participation, but with problems’, ‘reduced participation due to problems’ to ‘cannot participate due to problems’. The responses are scored from 0 to 25 for each question with 0 representing no problem and 25 maximal level of the problem. The total score for the OSTRC-0 is 100. The questionnaire shows high internal consistency, with a Cronbach’s α of 0.91.^35^

#### Perfectionism

Perfectionism is measured by the Frost Multidimensional Perfectionism Scale (FMPS).^36^ It consists of 35 questions, which are measured on a scale from 1 to 5 depicting the applicability of each statement to the participant. The questions are divided to give scores in six subcategories, namely: concern over mistake, personal standards, parental expectations, parental criticism, doubts about action and organisation (eg, ‘It is important to me that I be thoroughly competent in what I do’). A cut-off score of >29 points is used in clinical trials.^37^ Two subscales will be assessed in the present study due to these subscales showing acceptable to good internal consistency (personal standards=0.74; concern over mistakes=0.86).^38^

